### Outcome measures

An overview of all variables and questionnaires per assessment moment is given in Table 3. All questionnaires are (inter)nationally validated and Dutch normative data is available. Children and their families are enrolled into the study in groups of 6 to 10 families (3 to 5 families in the CHIP-group and 3 to 5 families in the CAU group). In both the CHIP-Family and the CAU condition, the first assessment will take place within 2 weeks before the CHIP-Family intervention (T1) and the follow-up post-assessment (T2) will take place 6 months after T1. Patients who are randomized into the CHIP-Family intervention group complete a social validity questionnaire assessing satisfaction with regards to the CHIP-program within 2 weeks after the intervention and at T2. All questionnaires are completed at home through a secure website.

**Table 3 Tab3:** Assessment instruments and moments of assessment

Instrument	Variable	Assessment moment		
		T1	Direct follow-up	T2
Primary outcomes				
Child Behavior Checklist (CBCL) [32]	Child behavioral/emotional problems	M, F		M, F
Symptom Checklist-90-Revised (SCL-90-R) [29]	Parental mental health	M, F		M, F
Secondary outcomes				
Rotterdam Quality of Life interview [30]	School days sick/absent	M, F		M, F, T
Rotterdam Knowledge Questionnaire [31]	Disease-specific knowledge and illness perception	M, F		M, F
Teacher Report Form (TRF) [32]	School functioning	-		T
Behavior Rating Inventory of Executive Functioning (BRIEF) [34, 35] or BRIEF-Preschool Version (BRIEF-P) [36]	Executive functioning	M, F		M, F, T
Adjusted Groningen Enjoyment Questionnaire [37]	Sports participation, enjoyment of physical activity	M, F		M, F, T
2 sports-related questions	Sports participation, enjoyment of physical activity	C		C
Penn State Worry Questionnaire (PSWQ) [49]	Parental worry	M, F		M, F
Nijmeegse Ouderlijke Stress Index verkort (NOSIK) [40]	Parental stress	M, F		M, F
Stress thermometer (DT-P) [50]	Parental stress	M, F		M, F
Child Health Questionnaire (CHQ-PF50) [51]	Quality of life of child and sibling	M, F		M, F
Short-form (36) Health Survey (SF-36) [52]	Quality of life of parents	M, F		M, F
Family Assessment Device, general functioning subscale (FAD) [53]	Family functioning	M, F		M, F
Medical record	Medical consumption	R		R
Social validity questionnaire	Satisfaction, attendance, and completion of CHIP-Family	–	M, F	M, F
Predictor variables				
Rotterdam Quality of Life interview [30]	Demographic variables	M, F		–
Medical record	Cardiac diagnosis	R		R
Life event subscale of the Cognitive Emotion Regulation Questionnaire, child version (CERQ-k) [44]	Life events	M, F		M, F

*M* Mother, *F* Father, *C* Child, *T* Teacher, *R* Medical records

T1 = baseline, Direct follow-up = within 2 weeks after CHIP-Family intervention (only for participants in intervention group), T2 = follow-up, 6 months after T1

#### Primary outcomes

##### Child behavioral/emotional problems

The problem section of the Child Behavior Checklist (CBCL) [27] 1,½-5 (100 items; for 4- and 5-year-olds) and CBCL/6–18 (120 items; for 6- and 7-year-olds) will be used to obtain standardized parent reports of emotional and behavioral problems in their child. Response categories range from 0 to 2, with higher scores indicating more emotional and/or behavioral problems. Adequate reliability and validity have been reported [28].

##### Parental mental health

The Symptom Checklist-90-Revised (SCL-90-R) [29] is a self-report scale (90 items; response categories: 1–5, higher score indicates more symptoms) which assesses 9 primary symptom dimensions: Somatization, Obsessive-Compulsive, Interpersonal Sensitivity, Depression, Anxiety, Hostility, Phobic Anxiety, Paranoid Ideation, and Psychoticism. Adequate reliability and validity have been reported for the Dutch version [29].

#### Secondary outcomes

##### School days sick/absent

Through the Rotterdam Quality of Life interview [30] parents and teachers will be asked how many days the child was absent from school and what the reasons for absence were.

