### Inclusion and exclusion criteria

Over a one-year period (September 2016 – September 2017) children and their families living in the Netherlands will be recruited. Eligible are all children who (1) underwent at least one invasive procedure (catheter intervention or surgery) for CHD and (2) are starting or attending kindergarten or primary school (first or second year) at the time of first assessment (as the children are approximately 4–7 years old). Exclusion criteria are: (1) child’s intellectual impairment (IQ < 70) as ascertained by previous standardized assessment or diagnosed by a clinician, (2) insufficient mastery of the Dutch language, and (3) prematurely born children (gestational age at birth < 37 weeks) with no other CHD than a patent ductus arteriosus.

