### Intervention

CHIP-Family consists of a parent module and a child module. Parents and children participate in a separate, but simultaneously given, 6-h group workshop. An overview of the content of the workshops is given in Table 2. Over the course of a 11-month period (Nov. 2016 – Sept. 2017) 11 workshops will be given to 3 to 5 families per workshop.

**Table 2 Tab2:** Outline of the CHIP-Family workshops

Health care professional(s)	Content
Parent workshop	
Psychologists	• Problem prevention therapy [48]. A DO ACT acronym is applied: **D**efine problem and turn into a specific goal; **O**ption brainstorm; **A**ssess pros and cons of various options; **C**hoose a strategy; **T**ake action and evaluate
	• Psychoeducation
	• General parenting skills
	• Specific parenting skills for children with CHD
Pediatric cardiologist	• Information on medical diagnoses, treatments, future issues (e.g., career, pregnancy), insurance, and healthy living (e.g., sports, diet)
Child workshop	
Psychologists	• Relaxation
	• Promoting autonomy
	• Strengthening self-esteem
	• Making friends
	• Problem solving skills
	• Positive thinking
Physiotherapists	• Playful, age-attuned sports exercises: warming-up, fitness, gross motor skills, balance, aiming, and catching

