### Statistical analysis

To test the effectiveness of CHIP-Family on the primary outcome measures (for parents: mental health [SCL-90-R]; for children: behavioral/emotional problems [CBCL]) repeated measures ANOVAs will be conducted, for parental and child outcomes separately. Group (CHIP-Family versus CAU) will be the between-subjects variable and assessment (T1 versus T2) will be the within-subjects variable. Likewise, repeated measures ANOVAs will be conducted for the secondary outcome measures.

Additional regression analyses will be conducted to investigate in what way demographic factors, medical factors, and life events moderate the effect of CHIP-Family on the primary outcome measures.

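### School absence: the planned T1-versus-T2 ANOVA uses a baseline that is near zero or undefined for children just starting school and does not exist for teacher reports

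*Protocol article*

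**What the plan says.** Under Secondary outcomes (School days sick/absent), the protocol article states that "parents and teachers will be asked how many days the child was absent from school", together with "what the reasons for absence were". In Table 3 (Outcome measures) the row "School days sick/absent" lists mother and father at T1, and mother, father and teacher at T2. The Abstract also says that teachers complete questionnaires at T2 only.

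Under Statistical analysis, the primary outcomes are analysed by repeated measures ANOVA with assessment (T1 versus T2) as the within-subjects variable, and "Group (CHIP-Family versus CAU) will be the between-subjects variable". The section continues: "Likewise, repeated measures ANOVAs will be conducted for the secondary outcome measures".

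Under Inclusion and exclusion criteria, eligible children "are starting or attending kindergarten or primary school (first or second year) at the time of first assessment".

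Three design features bear on the point. Families enrol in groups of 6 to 10, with 3 to 5 per arm and the same T1 and T2 timing in both arms (Outcome measures). Randomisation is stratified by school year (Recruitment and procedure). Under Intervention, "11 workshops will be given to 3 to 5 families per workshop", from November 2016 to September 2017. The article states no look-back period for the absence question and no count of possible school days.

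**The concern.** Days absent cannot exceed days on which the child could have attended. A child who has just started school at T1 has had few such days or none, so the T1 value says little or nothing about that child's tendency to be absent. The ANOVA nevertheless treats it as a baseline on the same scale as T2. The T1-to-T2 change within an arm then reflects time at school as well as absence, and subtracting so poor a baseline costs precision in the group-by-time test. For teacher reports there is nothing to subtract.

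The Background and Discussion name less school absence among the gains of the earlier CHIP-School programme, so readers will look for it here. At stake are the power and the readability of that one secondary result.

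**Working it through.** **The plan's own figure.** The article gives no figure for absence. Its sample size (d = 0.6, two-sided alpha .05, power .80) reproduces: 2 × (1.96 + 0.84)² / 0.6² = 43.6, so 44 per arm. The t-based version gives 44.6, so 45 per arm and 90 in total. The calculations below use 45 per arm.

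**One child (illustrative).** Take a constant absence rate of 5%, with 10 possible school days before T1 and 130 before T2. Expected counts are 0.05 × 10 = 0.5 and 0.05 × 130 = 6.5 days. The count rises by 6 days although the rate is unchanged.

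**Calendar (assumed dates).** Assume monthly mid-month workshops, T1 one week earlier, T2 182 days after T1, and a six-week summer closure from mid-July to late August, shifted by up to two weeks either way. Then 7 to 8 of the 11 T1-T2 windows overlap the closure and 4 to 5 contain all of it. This matters only if the look-back covers most of the six months.

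**Is the between-arm contrast biased?** This was simulated with 45 per arm in 11 calendar-matched groups, a six-month look-back, 4% absence and gamma-Poisson counts. The group-by-time test was a t-test on change, which is equivalent to the 2 × 2 interaction.

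| Starters | Change under usual care, no true change in rate (days) | Power at rate ratio 0.6, change in raw days | Power, change in days per 100 school days |
|---|---|---|---|
| 0% | -0.1 | 71% | 79% |
| 25% | +0.5 | 67% | 71% |
| 50% | +1.1 | 64% | 60% |

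With no treatment effect, the between-arm contrast averaged -0.02 to +0.01 days, with 3.5% to 4.6% rejection. At rate ratio 0.6 it was about -1.8 days. So the within-arm change carries exposure, the between-arm contrast is unbiased, and it responds to absence. Dividing by school days while still differencing helps little and not uniformly.

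**Which analysis gains power?** Assumed inputs: 45 per arm, 6% absence, rate ratio 0.6, six-month look-back, 20% starters, and absence tendency stable within a child.

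| Analysis | Power | Second run |
|---|---|---|
| Planned change test | 76% | 73% |
| T2 count model with offset, group only | 60% | 62% |
| T2 count model, T1 rate and low-exposure indicator, no offset | 91% | 92% |
| The same model with offset | 93% | 93% |

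The second run used frailty variance 1, 130 or 100 possible school days (60/40), and 0 to 29 days before T1 for starters.

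Full model against planned test: 93 - 76 = 17 points. Offset within the full model: 93 - 91 = 2 points, or 93 - 92 = 1. Adding the T1 information to the offset model: 93 - 60 = 33 points. With absence tendency only half shared between T1 and T2, the full model has about 69% against 43%, a gain of 26 points.

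**Short look-back.** With a look-back of about one month and 25% starters (4% absence), the change test had about 20% power and the full model about 35%.

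**Teacher reports.** Table 3 gives no T1 value, so a two-occasion ANOVA has no first occasion. This needs no assumption.

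**The case against.** The strongest reply is that efficacy is judged by the group-by-time contrast, not by the time effect. Both arms enrol in the same calendar groups with the same assessment timing, and school year is a stratification factor, so starters and school closures fall on both arms alike in expectation. That stands. A reader might infer that the comparison measures school exposure rather than absence; the documents do not support this, and the simulated contrast was centred on zero when the intervention did nothing.

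A second reply is that the absence item comes from a cited interview, condensed here to one sentence. Its look-back and any record of school start or possible school days may be given there. That stands too. The article states no such count, but it cannot be concluded that none is collected, and its absence from a condensed article is not a finding.

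A third reply is that the missing denominator explains little of the power loss. This is correct: an offset model with group only can do worse than the planned test (60% against 76%), and the offset adds only 1 to 2 points to the full model. The gain comes mainly from conditioning on T1 rather than differencing.

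What these replies leave in place is that the article itself fixes a two-occasion ANOVA for all secondary outcomes, applies it to a day count, and admits children for whom the first occasion is empty or nearly so. The mismatch is in the stated text.

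**Conclusion.** The point holds as a minor matter affecting one secondary outcome. For starters the T1 count is near zero or undefined, so the within-arm change cannot be read as a change in absence. Differencing against that baseline gives away precision, and the planned ANOVA cannot be applied to teacher-reported absence. No bias between arms is expected, and the primary outcomes and sample size are untouched.

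The teacher-report part and the existence of starters rest on the article alone. The power figures (76% to 93%, or 43% to 69%) rest on assumed absence rate, effect, look-back, share of starters and within-child stability, none of which the article gives. The direction was the same in the settings examined, but the size was not: with a look-back of about one month, power is low under either analysis.

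**What to change.** For this outcome, replace the T1-versus-T2 ANOVA with a between-arm comparison of T2 absence in a count model: negative binomial, or Poisson with robust standard errors. Adjust for the T1 absence rate where it exists, and include an indicator for children with little or no school exposure before T1. Use the same stated look-back at T1 and T2, with log possible school days as offset so that the result reads as a rate ratio. Do not adopt the offset without the baseline terms.

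Analyse teacher-reported absence at T2 only, with the same type of model; the parent-reported T1 rate could serve as the baseline covariate.

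Cost: one derived variable (possible school days, from school start date and calendar) or one added question per assessment, and a different model for one secondary outcome. Robust standard errors are slightly liberal at this sample size, with null rejection of about 4% to 7% in simulation; the report should say so.

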##### Disease-specific knowledge and illness perception

The Rotterdam Knowledge Questionnaire for Congenital Heart Disease [31] is used to assess parents’ knowledge about CHD and parents’ illness perception.

##### School functioning

The Dutch version of the Teacher’s Report Form (C-TRF) 1½-5 (100 items) [32] or the TRF/6–18 (120 items) [33] will be completed by the teacher of the child. The TRF assesses problem behavior (at school). Response categories range from 0 to 2, with higher scores indicating more emotional and/or behavioral problems.

##### Executive functioning

The Dutch Behavior Rating Inventory of Executive Functioning (BRIEF) [34, 35] (63 items; 2–5 years) and BRIEF-Preschool version (BRIEF-P) [36] (86 items; 5–18 years) will be used to assess executive functioning skills in daily life. Response categories range from 0 to 2, with higher scores indicating more problems.

##### Enjoyment of leisure-time physical activity

The Groningen Enjoyment Questionnaire (GEQ; 10 items; response categories 1–3, higher score indicates more enjoyment) [37, 38] is adjusted for parents and teachers and assesses enjoyment of physical activity. Children themselves answer two questions to assess how often they engage in physical activity and to assess enjoyment of physical activity.

##### Parental worry

The Penn State Worry Questionnaire (PSWQ; 16 items; response categories 1–5, higher score indicates higher level of worry) [39] assesses the excessiveness and uncontrollability of parental worry.

##### Parenting stress

The Nijmeegse Ouderlijke Stress Index verkort (NOSIK) [40, 41] (25 items; response categories 1–6, higher score indicates higher level of stress) measures stress due to parenting. Parents will also complete the Distress Thermometer (DT-P) [42] (40–42 items), which consists of a problem list and a thermometer on which parents are asked to rate their overall distress.

##### Quality of life of children and siblings

The Child Health Questionnaire Parent Form-50 (CHQ-PF50; 50 items) [43] is used to assess quality of life of the child with CHD and, if possible, of one sibling.

##### Parental quality of life

The Short-form (36) Health Survey (SF-36) [44] (36 items; score per domain 0–100, higher score indicates less disability) assesses eight health status domains: physical functioning, role limitations due to physical problems, bodily pain, general health, social functioning, role limitations due to emotional functioning, mental health, and vitality.

##### Family functioning

The general functioning subscale of the Family Assessment Device (FAD) [45] (12 items; response categories 1–4, higher total score indicates poorer functioning) assesses problem areas of family functioning.

##### Social validity

Through a questionnaire, parents will be asked about their satisfaction regarding CHIP-Family. Furthermore, data on attendance and completion of CHIP-Family will be recorded.

#### Predictors

##### Demographic variables

Demographic variables such as age, gender, and socio-economic status will be assessed through the Rotterdam Quality of Life interview [30].

##### Medical variables

Information about cardiac diagnosis, surgery, and intrusive procedures will be retrieved from medical records.

##### Life events

The ‘life events’ subscale of the Cognitive Emotion Regulation Questionnaire child version (CERQ-k) [44] is adjusted as such that parents can answer the questions about their child.

### Sample size calculation

To conduct a repeated measures ANOVA with two assessment moments, Cohen’s d of 0.6, an alpha of .05 (two-tailed), and a power of .80, a sample size of 90 patients is needed, of which 45 patients in the intervention group.

### Statistical analysis

To test the effectiveness of CHIP-Family on the primary outcome measures (for parents: mental health [SCL-90-R]; for children: behavioral/emotional problems [CBCL]) repeated measures ANOVAs will be conducted, for parental and child outcomes separately. Group (CHIP-Family versus CAU) will be the between-subjects variable and assessment (T1 versus T2) will be the within-subjects variable. Likewise, repeated measures ANOVAs will be conducted for the secondary outcome measures.

Additional regression analyses will be conducted to investigate in what way demographic factors, medical factors, and life events moderate the effect of CHIP-Family on the primary outcome measures.

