### Recruitment and procedure

Parents of 4- to 7-year-old children who receive treatment at the department of pediatric cardiology of the Erasmus Medical Center – Sophia Children’s Hospital and eligible members of the Dutch Patient Association for Congenital Heart Disease whose children receive treatment in a cardiac centre in the Netherlands will receive an information leaflet explaining the purpose and procedures of the study. Before inclusion, parents will receive a verbal explanation of the trial. After obtaining written parental informed consent, patients are randomly allocated to the CHIP-Family intervention or CAU group. To avoid a delay of more than 1 month between baseline assessment and the intervention, patients are randomized prior to the baseline assessment. Patients are allocated to the CHIP-Family intervention or CAU group by means of block randomization, performed by an independent researcher. Randomization will be stratified by CHD severity (limited to no residual heart defects or moderate to severe residual heart defects [after medical intervention]; see Table 1) and school year (kindergarten or primary school). To avoid bias, the researcher performing the assessments and analyses will be blinded. Considering the nature of the CHIP-Family intervention, it is not possible to blind the participants and the health care professionals providing the intervention.

**Table 1 Tab1:** Stratification factor “CHD severity”

Type 1	Type 2
Limited to no residual heart defects after medical intervention	Moderate to severe residual heart defects after medical intervention
Atrial Septal Defect (ASD)	ALCAPA (Anomalous Left Coronary Artery from the Pulmonary Artery)
Patent Ductus Arteriosus	Aortic Valve Stenosis
Pulmonary valve stenosis	Atrioventricular Septal Defect (AVSD)
Total Anomalous Pulmonary Venous Connection	Coarctation of the Aorta
Ventricular Septal Defect (VSD)	Complex Biventricular (e.g. Truncus Arteriosus, aortic arch defects)
	Double Inlet Ventricle – Fontan circulation
	Ebstein’s Anomaly
	Subvalvular Aortic Stenosis
	Tetralogy of Fallot (TOF)
	TOF with MAPCA (Main Aorta to Pulmonary Connecting Artery)
	Transposition of the Great Arteries

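### The primary repeated measures ANOVA is a change-score test; adjusting for T1, CHD severity and school year would be more efficient on the same data

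*Protocol article*

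**What the plan says.** For the two primary outcomes, CBCL and SCL-90-R, the Statistical analysis section states that "repeated measures ANOVAs will be conducted, for parental and child outcomes separately", and defines the model as follows: "Group (CHIP-Family versus CAU) will be the between-subjects variable and assessment (T1 versus T2) will be the within-subjects variable". It names no T1 covariate and no stratum term.

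Under Recruitment and procedure, "Randomization will be stratified by CHD severity" and also by school year, each with two levels. The same section states that "patients are randomized prior to the baseline assessment" and that "it is not possible to blind the participants and the health care professionals providing the intervention". Table 3 shows mothers and fathers as the raters of both primary outcomes at T1 and T2.

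The Sample size calculation uses "Cohen’s d of 0.6", two-sided alpha 0.05 and power 0.80, and concludes that "a sample size of 90 patients is needed, of which 45 patients in the intervention group". It gives no T1–T2 correlation and does not say whether d is scaled by the SD of the T2 score or of the change.

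**The concern.** With one pre- and one post-assessment, the group-by-assessment F statistic is the square of the two-sample t statistic on T2 minus T1. Subtracting T1 in full over-corrects when T1 and T2 are imperfectly correlated, because the noise in T1 is added to that in T2. Entering T1 as a covariate lets the data set the weight, and for a randomised comparison this is normally the more precise choice.

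The sample size sits at the planned 80% with no margin, so precision given up in the analysis is not made good elsewhere. The two stratification factors are also known for every child, yet the stated model leaves them out.

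**Working it through.** **Inputs from the article.** d = 0.6, two-sided alpha 0.05, power 0.80, 90 in total with 45 per arm (Sample size calculation); the ANOVA terms (Statistical analysis); two stratification factors (Recruitment and procedure). **Assumed.** rho, the T1–T2 correlation, taken over a range; and the SD to which d refers, taken both ways.

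**Step 1: the article's own figure.** For a two-sample t-test with n per arm, the noncentrality is d × sqrt(n/2) on 2n − 2 df. With n = 45 this is 0.6 × sqrt(22.5) = 2.85 on 88 df, and power is 0.804. With n = 44, power is 0.795. So 45 per arm, 90 in total, reproduces. Repeated-measures formulas with f = 0.6/2 = 0.3 and rho = 0.5 give 24 in total (interaction) or 68 (between factor), so 90 is the plain two-sample figure. It matches the planned change-score test if d is on the change SD, or if d is on the T2 SD and rho = 0.5.

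**Step 2: variances.** In units of a common T1 and T2 variance:

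- change score: 2(1 − rho)
- T2 adjusted for T1: 1 − rho²
- ratio, adjusted to change: (1 + rho)/2, which is below 1 for every rho below 1

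The ratio needs equal variances, but the direction does not. With SDs s1 and s2, the change-score variance minus the adjusted variance is (s1 − rho × s2)², which is never negative.

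**Step 3: power at 45 per arm, d on the T2 SD.** Effective d is 0.6/sqrt(2(1 − rho)) for change and 0.6/sqrt(1 − rho²) for the adjusted model. The adjusted model is charged 3 df (T1, severity, school year).

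| rho | Effective d, change | Effective d, adjusted | Power, change | Power, adjusted | Total N for 80%, change / adjusted |
|---|---|---|---|---|---|
| 0.3 | 0.6/sqrt(1.40) = 0.51 | 0.6/sqrt(0.91) = 0.63 | 0.66 | 0.84 | 126 / 82 |
| 0.5 | 0.6/sqrt(1.00) = 0.60 | 0.6/sqrt(0.75) = 0.69 | 0.80 | 0.90 | 90 / 68 |
| 0.7 | 0.6/sqrt(0.60) = 0.77 | 0.6/sqrt(0.51) = 0.84 | 0.95 | 0.98 | 56 / 48 |

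**Step 4: power at 45 per arm, d on the change SD.** The change-score test has 0.80 at any rho. The adjusted model has effective d = 0.6/sqrt((1 + rho)/2) and power 0.94, 0.90, 0.86 and 0.82 at rho 0.3, 0.5, 0.7 and 0.9.

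**Step 5: simulation.** There were 4,000 trials per setting, N = 90, with stratified blocks and an assumed 10% of outcome variance due to strata, equal at T1 and T2. Power for change against adjusted was 0.66 and 0.86 (rho 0.3), 0.81 and 0.92 (rho 0.5), and 0.95 and 0.98 (rho 0.7). These are close to Step 3, which gives the strata no explanatory value, so nearly all the gain comes from T1. With no effect, type I error at rho 0.3 to 0.9 was 0.045–0.057 for the unstratified change test and 0.044–0.057 for the adjusted model.

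**Step 6: if knowledge of allocation alters T1.** Assume a 0.2 SD shift in T1 in one arm and no T2 effect. The simulated change score is biased by 0.20 SD, with false positives of 15% (rho 0.5) and 23% (rho 0.7). The adjusted model is biased by 0.09 and 0.13 SD, with false positives of 7% and 14%.

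**The case against.** The strongest objection concerns T1 itself. It is measured after randomisation, by parents who cannot be blinded and who rate both primary outcomes. Adjusting for a variable that allocation may have influenced is not automatically safe, and the article does not say whether families know their arm by then. This stands as a condition on the fix. It does not rescue the planned test, which uses the same T1 at full weight and does worse in Step 6. The exception is a reporting shift that persists unchanged to T2. The change score would then be unbiased, while the adjusted estimate would carry 0.2 × (1 − b), where b is the within-stratum slope (rho − 0.1)/0.9 in that simulation: 0.11 SD at rho 0.5 (b = 0.44) and 0.07 SD at rho 0.7 (b = 0.67).

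The size of the gain is also open. If d is on the change SD, the planned test keeps its 80% at every rho and the 0.66 figure does not arise. At high rho the two methods nearly agree.

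Three stronger readings are tempting but not supported:

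- **Leaving out the strata invalidates the inference.** Simulated type I error was near nominal. Stratum effects that are equal at T1 and T2 cancel in a change score.
- **The plan excludes families with an incomplete pair.** A classical repeated measures ANOVA behaves that way, but the article states no missing-data rule, and one may sit in an analysis plan that is not shown. A plain regression of T2 on T1 also loses anyone without T2: with 20% loss and rho 0.5, power falls to 0.71 (change) and 0.83 (adjusted).
- **Effectiveness might be read from the group main effect, which would dilute it with T1.** The interaction is the natural reading of the stated design.

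**Conclusion.** The planned primary analysis is valid but less efficient than a T1-adjusted model on data the trial already collects. At 45 per arm and an assumed rho of 0.5, power is about 0.80 against 0.90 on either scaling of d. For rho from 0.3 to 0.7, the gain runs from about 18 points down to 2 with d on the T2 SD, and from about 13 down to 6 with d on the change SD. These figures assume equal T1 and T2 variances and a T1 unaffected by allocation. Including severity and school year aligns the analysis with the randomisation and is a minor efficiency point.

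The change should not be presented as free. It uses 3 df, which is trivial: at rho = 0 the adjusted model has power 0.803, against 0.804 for an unadjusted t-test on T2. It also rests on the condition about T1.

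**What to change.** For each primary outcome (CBCL and SCL-90-R), define the primary estimate as the group difference at T2, with 95% CI, from a model of T2 on group with T1 score, CHD severity and school year as covariates.

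A likelihood-based mixed model on T1 and T2 with the same stratum terms may be used instead, so that participants with one missing assessment still contribute. It reaches the T1-adjusted precision only if T1 means are constrained to be equal across arms. Without that constraint, its group-by-assessment contrast returns to the change score in complete data.

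State whether T1 is completed before families learn their allocation. If it is not, do not impose the constraint, and acknowledge that both the covariate-adjusted and the change-score estimates depend on T1.

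The cost is a change of wording in the analysis plan and 3 df, with no additional data. How mother and father reports are combined, and how the two age versions of the CBCL are handled, are separate matters that this change does not settle.
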